#### Leaving a relationship because it felt unhealthy, unsafe or abusive among those reporting either RC or IPV

Participants, who report ever experiencing physical or sexual IPV or RC at baseline will be asked if, “in the last three months, have you left a relationship because it felt unhealthy, unsafe, or abusive?” This outcome will be assessed only at T2 and T3, and is based on a similar measure used in U.S.-based ARCHES trial [23, 24].

#### Demographics and other potential confounders

Demographics and potential confounders will include age, parity, food insecurity, marital status, highest level of education attended, and language of survey administration. Age will be assessed as a continuous measure. Other measures will be categorical in nature. Parity will be classified as either having no live births, having one live birth, or having multiple live births. Past month food insecurity will be assessed as a binary (yes/no) item based on the question, “In the last 30 days, did you or any members of your household go without eating the whole day because there was not enough food?” Women both formally married and those cohabitating with a male partner will be considered married based on common practice. Highest level of schooling attended will be classified as primary or lower, secondary, or post-secondary.

### Power calculations and sample size

Based on the pilot data from 143 female FHOK patients ages 15–49 years, prevalence of RC within the past 12 months was estimated at 17.1%. In a large U.S. cRCT, clients receiving the ARCHES intervention experienced a 0.4 reduction in odds (equivalent to an 8 percentage point reduction in intervention group reporting) of RC during the prior 3 months [23]. The present study is designed to achieve 80% power to detect a reduction of this magnitude (OR 0.4) related to past 3-month RC experience. Calculations assumed three control and three intervention clusters. Cluster size was assumed to differ in the range of 50–250 individuals per cluster, with a mean number per cluster of 100; the coefficient of variation for cluster sizes was thus set at 0.5. We anticipated low intra-class correlation (ICC) based on previous ARCHES trials (ICC < 0.01%) [23]. To be somewhat more conservative, we assumed an ICC of 0.1%. Under these parameters, the required average cluster size was 68, for a total of 204 control and 204 intervention participants (total required *N* = 408) retained at final follow-up. In previous ARCHES trials, retention was > 90% at 3-months follow-up; we assumed 85% retention at 3-months follow-up relative to baseline and 75% retention at 6-months follow-up relative to baseline, for an initial minimum N of 544. Our target final sample of 600 individuals exceeds the sample size required based on this conservative calculation.

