### Primary outcomes

#### Reproductive coercion (RC)

Recent (prior 3 months) experience of RC will be assessed using a 9-item scale on specific RC behaviors including pregnancy coercion (e.g. “Has a male partner ever tried to force or pressure you to become pregnant when you did not want to be pregnant?”), and birth control sabotage (e.g. “Has a partner ever destroyed, hidden, or taken away your family planning method?”). RC is assessed primarily as a binary (yes/no) outcome based on a positive response to any RC experiences. Additionally, a summary score of the number of RC items experienced (Score 0–9) will be assessed in exploratory analyses. Items for this measure were adapted from those in the RC scale developed in the U.S. (Cronbach alpha = 0.74) [25] based on formative research and cognitive interviewing.

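### The 80% power for past-3-month reproductive coercion uses a 12-month prevalence as the control risk, so for OR 0.4 it is a best case

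*Protocol article*

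**What the plan says.** All of this is in the protocol article.

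- **Control rate.** Under Power calculations and sample size, the only local figure comes from 143 pilot patients: "prevalence of RC within the past 12 months was estimated at 17.1" per cent.
- **Target.** The same section says: "The present study is designed to achieve 80% power to detect a reduction of this magnitude (OR 0.4) related to past 3-month RC experience".
- **Source of the effect.** A large U.S. cluster trial is cited, in which "clients receiving the ARCHES intervention experienced a 0.4 reduction in odds". A parenthesis adds that this is "equivalent to an 8 percentage point reduction in intervention group reporting".
- **Outcome window.** Under Primary outcomes: "Recent (prior 3 months) experience of RC will be assessed using a 9-item scale". Table 1 gives the same 3-month window.
- **Other inputs.** Three clinics per arm, coefficient of variation (CV) of cluster size 0.5, ICC 0.1%, and 75% retention at 6 months.
- **Results.** 68 per clinic, 204 per arm, 408 retained and 544 enrolled. The target of 600 is said to be more than this calculation needs, and the calculation is called conservative.

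**The concern.** The prevalence and the outcome cover different periods. The power statement concerns 3-month RC, the only prevalence offered covers 12 months, and the section gives neither a 3-month figure nor a conversion. If 17.1% went into the calculation unchanged, the control risk is probably too high. For a fixed odds ratio, a lower control risk means fewer events, a smaller absolute difference and less power. Readers would then take the trial to be better powered on a primary outcome than its own inputs support.

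A smaller point concerns the effect. A reduction in odds of 0.4, read literally, is OR 0.6, while the design target is OR 0.4. The 8-point figure is also not the difference that the calculation uses.

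**Working it through.** **Inputs from the protocol article.** Control risk p1 = 0.171; OR 0.4; power 80%; alpha 0.05, taken as two-sided because the Data analysis section ties it to 95% confidence intervals; k = 3 clinics per arm; ICC = 0.001; CV = 0.5; retention 75%; target 600.

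**Step 1: reproduce the plan's figure.**
- Control odds: 0.171/0.829 = 0.2063. Times 0.4 = 0.0825, so p2 = 0.0825/1.0825 = 0.0762. The difference is 9.5 points.
- Per-arm n without clustering: n = [1.96·√(2·p̄(1−p̄)) + 0.8416·√(p1(1−p1) + p2(1−p2))]² / (p1−p2)², with p̄ the mean of p1 and p2. This gives 188.1.
- Design effect: DE = 1 + [(1 + CV²)·m − 1]·ICC. Setting 3m = n·DE gives m = n(1 − ICC)/(k − n·ICC·1.25) = 188.1 × 0.999/(3 − 0.235) = 67.97, so 68.
- 6 × 68 = 408, and 408/0.75 = 544.

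All the published figures are recovered with the 12-month 17.1% in the place of the 3-month control risk.

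**Step 2: direction.** The past 3 months lie within the past 12, so in the same women the 3-month prevalence is at most 17.1%. At 408 retained, DE = 1.084 at m = 68, the effective n is 204/1.084 = 188.2 per arm, and power is 80.0%. Any lower control risk with OR 0.4 gives less.

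**Step 3: the margin from enrolling 600.** 600 × 0.75 = 450 retained, or 225 per arm (m = 75, DE = 1.093, effective n = 205.9). Solving for the control risk that gives 80% power at OR 0.4 yields about 15.5%.

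**Step 4: range.** No 3-month prevalence is given, so the values below 17.1% are assumptions. Power = Φ{[√n_eff·(p1−p2) − 1.96·√(2·p̄(1−p̄))]/√(p1(1−p1) + p2(1−p2))}, OR 0.4 throughout:

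| 3-month control risk | Intervention risk | Power, 408 retained | Power, 450 retained |
|---|---|---|---|
| 17.1% | 7.6% | 80% | 83% |
| 15% | 6.6% | 75% | 79% |
| 12% | 5.2% | 66% | 70% |
| 10% | 4.3% | 58% | 62% |
| 8% | 3.4% | 49% | 53% |

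These compare two follow-up proportions, the approach that reproduces the plan's sample size. They are not powers for the difference-in-differences mixed model in the Data analysis section.

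**Step 5: the effect wording.** At 17.1%, OR 0.6 means 11.0% (6.1 points) and OR 0.4 means 7.6% (9.5 points). OR 0.4 equals an 8-point drop at a control risk of about 14.2%.

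**The case against.** **No 3-month prevalence is documented.** A reader might infer that the 80% is simply not delivered, or that the trial has only even odds of detecting OR 0.4. The document does not support either reading. Even odds corresponds to one assumed control risk, 8%. At 15.5% the planned 450 would still give about 80%. The ceiling of 17.1% also binds only for the same women: the trial requires a male sexual partner in the past 3 months, whereas the pilot sample is described only as female clinic patients aged 15–49, so the trial's rate could differ. This makes the size of the loss conditional. It does not supply the missing 3-month input.

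**The effect scale matters.** For a fixed 8-point drop, a lower control risk raises power: 12% against 4% gives 82% at 408 and 85% at 450. The loss therefore holds for the OR 0.4 target, which is the one the plan names.

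**The inputs are not uniquely identified.** An 8-point drop from 12.4% (OR about 0.33) also gives 68 per clinic. The pair of 17.1% and OR 0.4 is the natural reading because the section states both, but the reproduction alone does not prove it.

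**The effect statements may not conflict in substance.** A reader might infer three incompatible targets. However, the 8 points belong to the U.S. trial, whose control rate is not given, and they agree with OR 0.4 near 14.2%. The reduction of 0.4 is most likely loose wording for OR 0.4, which the next sentence names. What stands is a wording fault.

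**Conservative is partly earned.** The ICC is above, and the assumed retention below, what earlier trials showed, and 600 does exceed 544. Neither addresses the recall window.

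**Conclusion.** The concern stands as a mismatch of input and outcome: a 12-month prevalence serves as the control risk for a 3-month outcome, and the stated 80% depends on it. The arithmetic itself is correct.

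With OR 0.4 held fixed, and for women like those in the pilot, 80% at 408 retained requires the 3-month prevalence to equal the 12-month one. The 600 target tolerates a fall only to about 15.5%. For assumed 3-month risks of 8% to 12%, power is about 49% to 66% at 408 retained and 53% to 70% at 450. This rests on the plan's ICC and CV, a normal approximation and a comparison of follow-up proportions. The stated power is therefore unsupported for the outcome tested and probably optimistic; how far cannot be settled from the document.

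The odds-reduction wording and the U.S. 8-point figure are a minor clarification and do not show that the plan had several targets.

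**What to change.** 1. Replace 17.1% with a past-3-month control risk. The pooled, arm-blind baseline (T1) prevalence is already collected and would serve, if control-arm risk is assumed stable to follow-up. Otherwise state a range.
2. Give the target once, as OR 0.4 with its control and intervention proportions. Correct the odds-reduction wording, and label the 8 points as the U.S. trial's result, not the difference used here.
3. Restate the power, or the OR detectable with 80% power, for the 408 to 450 women expected at 6 months.
4. Keep the conservative label, and the statement that 600 is more than required, only if they still hold.

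The cost is one recalculation, some rewording and probably a less favourable stated power. No participants are added, and the design and analysis do not change.

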### Data analysis

We will adopt a difference-in-differences approach utilizing a multilevel, mixed-effects generalized linear regression, with logistic specifications for binary outcomes and linear specifications for continuous or scale outcomes, to evaluate associations between ARCHES intervention exposure and primary and secondary outcomes overtime. Longitudinal models will have fixed effects including time (baseline or follow-up), treatment arm, clinic, selected covariates, and a time and treatment interaction to indicate the treatment effect. These models will also take into account clusters (i.e. clinics) and clustering within clinics using nested random effects specifications to account for repeated measurements over time of individuals nested within clusters. The comparisons of outcomes at a single time point (e.g. immediately post-intervention) will use a similar multilevel mixed-effects regression approach, with single-level random effect specifications only for clinic, and only a fixed treatment effect (rather than time by treatment comparison). Final analyses will adjust for potentially relevant covariates (age, parity, food insecurity within the past 30 days, marital status, highest level of education attended, language of survey administration), in addition to time and treatment condition. Descriptive and bivariate analyses will be used to assess frequencies of and differences in demographics by treatment and loss to follow-up. Any characteristics identified as significantly associated with treatment or loss to follow-up at the *p* < 0.20 threshold will be considered as potential covariates (fixed effects) in adjusted models assessing effects of the intervention. Backwards selection at *p* < 0.20 will be used to finalize inclusion of potential covariates in regression models. Collinearity of covariates will be assessed, and highly collinear covariates may be removed from final models.

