The primary analyses will use an intent-to-treat approach and analyze all subjects according to treatment group. Exploratory analyses will also be run stratified by age group (adolescent girls and young women age 16 to 24; adult women age 25 to 49). Missing data on demographics and birth history may be computed where alternate data is available (e.g. calculating age from date of birth if age is not provided); however, no missing data will be imputed. All scales to be used as outcomes will be assessed for internal reliability at baseline using exploratory factor analysis and Cronbach’s alpha. If scales are identified as multifactorial or not internally reliable, they may be modified to more accurately reflect the intended construct and/or be presented as individual item outcomes. An α level of 0.05 (i.e. 95% confidence intervals exclusive of one) will be considered the threshold for statistical significance in all analyses. Analyses will be conducted using STATA version 14.2® (StataCorp LLC, 2015) [48] and SAS version 9.4® (SAS Institute Inc., 2018) [49].

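### The sample size is built for one comparison of two follow-up proportions, so the stated 80% power does not describe the planned difference-in-differences test of reproductive coercion

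*Protocol article*

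**What the plan says.** **Sizing** (Protocol article, Power calculations and sample size). The base rate comes from pilot data: "prevalence of RC within the past 12 months was estimated at 17.1" per cent. The section continues: "The present study is designed to achieve 80% power" "to detect a reduction of this magnitude (OR 0.4) related to past 3-month RC experience". On clusters it says "Calculations assumed three control and three intervention clusters", with a cluster-size coefficient of variation of 0.5 and an ICC of 0.1%. The result is "Under these parameters, the required average cluster size was 68, for a total of 204 control and 204 intervention participants". Allowing for 75% retention at 6 months gives 544 enrolled, and the section closes: "Our target final sample of 600 individuals exceeds the sample size required based on this conservative calculation".

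**Analysis** (Data analysis). "We will adopt a difference-in-differences approach utilizing a multilevel, mixed-effects generalized linear regression". The time-by-treatment interaction is named as the treatment effect, with nested random effects for repeated measurements on women within clinics. Time is described with two levels, baseline and follow-up.

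**Outcome.** Table 1 lists RC as a change from baseline. The Hypotheses section refers to effects at both 3 and 6 months.

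**The concern.** The power section mentions no baseline measurement, no within-woman correlation and no interaction effect. A difference between two changes carries the sampling error of the baseline as well as that of the follow-up. It is more precise than a single follow-up comparison only when the two measurements are strongly correlated. The 80% was therefore worked out for a different test from the one the plan will use on this primary outcome.

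What is at stake is how a null result on RC will be read. Someone who takes the 80% at face value would treat a null as fair evidence against an odds ratio of 0.4. If actual power is nearer 60-70%, that reading is too strong.

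**Working it through.** **Inputs from the protocol.** Control proportion p1 = 0.171; OR 0.4; two-sided alpha 0.05; power 80%; three clinics per arm; CV 0.5; ICC 0.001; 75% retention; 600 enrolled, so 300 × 0.75 = 225 retained per arm.

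**Step 1: the plan's own figure.**
- Odds in the intervention arm: 0.4 × 0.171/0.829 = 0.0825, so p2 = 0.0762. Difference d = 0.0948; mean proportion 0.1236.
- Binomial variances: a = 0.171 × 0.829 = 0.1418; b = 0.0762 × 0.9238 = 0.0704.
- n per arm = [1.96 √(2 × 0.1236 × 0.8764) + 0.8416 √(a + b)]² / d² = (0.9123 + 0.3877)² / 0.0948² = 188.1.
- Design effect at m women per clinic: 1 + (1.25m − 1) × 0.001, which is 1.084 at m = 68. Solving 3m = 188.1 × design effect gives m = 67.97.
- Hence 68 per clinic, 204 per arm, 408 retained, and 408/0.75 = 544.

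The protocol does not name its formula, so this is inferred from the match. One-sided (53), continuity-corrected (76), log-odds-ratio (72), 8-point-difference (105) and 4-df t (130) versions all miss 68. Unpooled variance or CV = 0 gives 67; both are also single-time-point normal formulas.

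**Step 2: the planned contrast, baseline to one follow-up.** Assume both arms start at 17.1%, work on the linear scale, and let r be the within-woman correlation.
- Variance of change, control: 2a(1 − r).
- Variance of change, ARCHES: a + b − 2r√(ab), with √(ab) = 0.0999.
- V is the sum of the two. Relative to a + b = 0.2122, V is 1.88, 1.65, 1.43 and 1.20 times as large at r = 0.2, 0.3, 0.4 and 0.5.
- Power = Φ(d/SE − 1.96), with SE = √(V × k/225). Two values of k bracket the answer: the full design effect at 75 per clinic, 1 + (1.25 × 75 − 1) × 0.001 = 1.093, and 1, which lets stable clinic effects cancel from the change.

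Example at r = 0.3: V = 0.3507. With k = 1, SE = 0.0395, d/SE = 2.40, power 67%. With k = 1.093, SE = 0.0413, d/SE = 2.30, power 63%.

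**Step 3: both follow-ups pooled as one level.** Assume the same r between every pair of occasions and the same p2 at both follow-ups. The control variance becomes 1.5a(1 − r). The ARCHES variance becomes a + b(1 + r)/2 − 2r√(ab). At r = 0.3 the sum is 0.1489 + 0.1276 = 0.2764.

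| r | One follow-up, 225 per arm | Both follow-ups pooled, 225 per arm |
|---|---|---|
| 0.2 | 58-61% | 68-72% |
| 0.3 | 63-67% | 74-77% |
| 0.4 | 70-73% | 80-83% |
| 0.5 | 77-81% | 86-89% |

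The lower figure uses the full design effect; the upper lets stable clinic effects cancel. For comparison, the single-time-point normal test at 225 per arm has about 84% (unpooled variance).

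**Step 4: break-even.** At 204 per arm, the one-follow-up interaction reaches 80% at r of about 0.54 to 0.6. At 225 per arm, it does so at about 0.49 to 0.54.

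**Step 5: few-cluster sensitivity only.** With a t reference on 6 − 2 = 4 df (critical value 2.776) and 225 per arm, the single-time-point contrast has about 61% power. The interaction at r = 0.3 has about 42-45%.

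**The case against.** Several points on the other side are sound and limit the claim.

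- **The arithmetic is right.** 68, 204, 408 and 544 all reproduce. The fault is in which test was sized.
- **The direction depends on r.** The documents give no r, and above the break-even the interaction has more than 80% power. A reader might infer that the trial is underpowered whatever r is; the figures do not show that.
- **The pooled reading is open.** The two-level description of time can be taken to pool the 3- and 6-month surveys, and pooling reaches 80% near r = 0.4. The Hypotheses section points instead to effects at each time. The text does not settle it, so both readings belong in the statement.
- **Degrees of freedom.** A reader might infer that the planned test has at most 4 df, or 2 if the pairs are kept. The Data analysis section names no small-sample reference, includes clinic as a fixed effect and states no clinic-by-time random term, so the interaction it describes is a within-woman contrast. The calculation also does count six clinics, through the design effect. The 4-df figures show what a clinic-level test would give, not what the protocol specifies.
- **The word conservative.** It has a basis: the ICC is at least ten times that reported for earlier trials, and retention is set below theirs. It is justified for those two assumptions, but not as a description of power for the planned test.

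What remains is the mismatch. The power section contains nothing from which 80% for the interaction could follow.

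**Conclusion.** The concern holds as a mismatch between the test that was sized and the test that is planned. The stated 80% belongs to a single follow-up comparison. For the planned one-follow-up interaction at 225 retained per arm, power is about 58-73% for r from 0.2 to 0.4, and reaches roughly 80% near r = 0.5. With both follow-ups pooled it is about 68-83% over the same r.

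These figures rest on the plan's 17.1%, OR 0.4 and ICC 0.1%, normal critical values, equal baselines, a linear approximation to the logistic interaction, and an assumed range for r. They take 17.1% as given; that it is a 12-month rate used for a 3-month outcome is a separate matter. The difference-in-differences model itself is not in question, and neither is the enrolment target.

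**What to change.** 1. Recompute power for the time-by-treatment interaction at 225 retained per arm, over a stated range of r, and print that range in place of the unqualified 80%.
2. State whether the 3- and 6-month surveys are tested separately or pooled, and give the power for that choice.
3. If r or the ICC is estimated from trial data, do so in a way that does not absorb the arm effect, for example by taking the ICC from baseline data only. A follow-up ICC that ignores arm would pick up the treatment difference. At 17.1% against 7.6% that alone gives about (0.0948/2)² / (0.1236 × 0.8764) = 0.02, twenty times the assumed 0.001.
4. Add a few-cluster figure, such as the 4-df result, labelled as a sensitivity.
5. Limit the word conservative to the ICC and retention assumptions.

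The cost is a short calculation and some rewording. The downside is a less favourable stated power. No extra enrolment and no change to the analysis model is proposed.

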### Participants – ethics, recruitment, eligibility, and informed consent

#### Ethics approval

This research protocol was initially approved by the Population Council institutional Review Board (IRB) on January 18, 2017 (Protocol Number 797), the Human Research Protections Program (HRPP) at the University of California San Diego on February 7, 2017 (Protocol Number 170084), and by the Kenyatta National Hospital-University of Nairobi Ethics & Research Committee (KNH-UON ERC) on March 2, 2017 for 1 year. Approval is sought from all ethics committees for amendments and annual renewals, which are currently approved through January 9, 2021. Research ethical and safety protocols for this study adhere to recommendations issued by the World Health Organization (WHO) for research on violence against women [43]. Ethics review by all three institutions determined that the proposed research poses no more than minimal risk to participants as the intervention provided is “reasonably commensurate with those inherent in their actual or expected situations” [44].

#### Recruitment and eligibility

Upon entering the clinic, female patients check-in for their appointment at the front-desk with the clinic receptionist who will offer the option to participate in a “women’s health study.” If interested in hearing more, the patient will be referred to a trained RA to complete recruitment. The RA will escorts the patient, alone without accompanying male partners or family members, to a location within the clinic that ensures visual and auditory privacy where they provide a brief description of the study and conduct eligibility screening. To be eligible for study enrollment, the patient must indicate that they are a) visiting the clinic “for family planning or are interested in receiving family planning” at their appointment that day, b) biologically female, c) age 15–49 years, d) not currently pregnant (self-report), e) not sterilized (self-report), f) have a male partner with whom they have had sex in the past 3 months, g) able to safely participate in a private interview without accompanying male partners or family members present, h) available for the 45 min necessary to conduct the interview, i) have no plans to move out of the area in the next 6 months, and j) have a mobile phone that can be safely used for re-contacting for follow-up surveys. As clients are recruited from general care, to be eligible for inclusion in follow-up surveys, participants must complete the immediate post-intervention (i.e. exit survey) and report having received contraceptive counseling on their exit survey.

If the patient declines to participate or is ineligible, the RA will walk them back to the waiting room and ensure that the patient did not lose their place in the queue for services. If eligible and interested, patients will receive a detailed explanation of the study, including estimated time required (30–45 min for baseline, 15 min for exit survey), compensation structure, that participation is completely voluntary and will not affect the care they receive, and that responses will be kept completely confidential. With permission, the RA will then administer informed consent and, after obtaining written informed consent, conduct the baseline survey in the language of the participants’ choosing (English or Kiswahili). After survey completion, RAs will remind participants of the 15-min exit survey to be completed before they leave the clinic and then walk participants back to the waiting room for their appointment ensuring they did not lose their place in the queue. After their visit with a provider, and before leaving the clinic, participants will meet with the RA for completion of the immediate post-visit exit survey. At the end of the exit survey, the RA will thank the participants for their time, schedule their 3-month follow-up survey, validate their contact information, and obtain an alternate contact in case they are unreachable.

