### Assignment of clinics to treatment conditions

As ARCHES facilitates changes in providers’ contraceptive service delivery to all female patients seen, individual random assignment of patients is not possible. Instead, assignment at the clinic level is required. All FHOK community-based clinics within and around the Nairobi area were enumerated (*N* = 6) by UCSD researchers and assigned to treatment or control condition in matched-pairs (*n* = 3 intervention, 3 control) by the UCSD and FHOK, with pairings determined based on those clinics most closely matched on patient volume, patient characteristics (i.e. wealth, age, services sought), and community type (slum vs non-slum). Random assignment within pairs was not acceptable to program implementers due to the reduced feasibility of providing regular support to ensure faithful, high-quality implementation to providers in distal clinics; i.e., those clinics closest to FHOK headquarters in southeast Nairobi were more likely to be assigned to the treatment condition. Participants self-assign to the treatment or control condition based on the clinic they visit for contraceptive services and enroll into the study by Population Council research assistants (RAs). No blinding of participants or providers will occur.

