### Data collection

#### Time points

Patients in both treatment and control groups will complete surveys at baseline (T1) prior to their clinical visit, immediately after their visit before exiting the clinic (exit survey), 12–16 weeks post-visit (3-month follow-up survey, T2), and 24–26 weeks post-visit (6-month follow-up survey, T3). RAs will be trained via a 5-day training, led by Population Council, that provides education on the ARCHES intervention, RC and IPV, responding to and referring participants that become upset during the interview, study protocols, and data collection forms. All surveys will be completed in-person via RAs reading all questions and responses aloud and recording responses using a tablet computer (Fig. 1. Study design; Table 1. Outcome measures).

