#### Patient accrual and study flow

Six clinics, each treated as their own cluster, were matched-paired and allocated to a treatment group (3 intervention, 3 control). From each clinic, women will be approached for study recruitment; women will be excluded in the enrollment due to ineligibility or because they declined to participate, with the rest completing the baseline survey. See Fig. 1. Study design.

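### Primary uptake outcome is compared between non-randomised clinics without planned adjustment for whether women came for family planning or were only interested in it

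*Protocol article*

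**What the plan says.** **Allocation.** The protocol article, under Assignment of clinics to treatment conditions, states that "Random assignment within pairs was not acceptable to program implementers". Clinics nearer the operator's headquarters were more likely to be treated. It adds that "Participants self-assign to the treatment or control condition based on the clinic they visit for contraceptive services". Clinics were paired on volume, community type and patient characteristics, and the last of these includes the kinds of service patients come for.

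**Recruitment.** Under Recruitment and eligibility, "female patients check-in for their appointment at the front-desk with the clinic receptionist who will offer the option to participate in a" study described only as one on women's health. Interested women go to a research assistant, who screens them in private. Criterion (a) has two limbs: the woman is visiting "for family planning or are interested in receiving family planning” at their appointment that day". The same section confirms that clients come from general care.

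**Outcome and model.** Uptake of a modern method is a primary outcome: whether the woman received a method at that visit, asked in the exit survey. Table 1 marks it as analysed on its follow-up value only. Under Data analysis, outcomes at a single time point use a mixed model "with single-level random effect specifications only for clinic, and only a fixed treatment effect (rather than time by treatment comparison").

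**Covariates.** Six are named: age, parity, food insecurity, marital status, education and survey language. The section on demographics and other potential confounders lists the same six.

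**The concern.** Whether a woman came for contraception is plausibly one of the strongest predictors of leaving with a method that day. Criterion (a) pools women who did with women who did not. Arms were not randomised and women sort themselves by clinic, so nothing in the design makes the split between the two limbs equal across arms. It could differ because the clinics serve different patients, or because different women are offered or accept the study.

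Reproductive coercion and partner violence have a baseline value and a difference-in-differences contrast, which removes a stable difference in level between arms. Uptake has neither. Its treatment coefficient is a plain between-arm comparison adjusted for six variables, and visit reason is not one of them. At stake is whether a positive (or null) result on one of the three primary outcomes reflects the counselling or the mix of women enrolled.

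**Working it through.** **The plan's own figure.** The sample size is for reproductive coercion; none is given for uptake. It reproduces. An odds ratio of 0.4 on 17.1% gives 7.6%, which needs 189 per arm before clustering (pooled two-proportion test, two-sided 0.05, 80% power). With ICC 0.001, CV 0.5 and three clusters per arm, the cluster size is m = 189 × 0.999 / (3 − 189 × 1.25 × 0.001) = 68.3, against 68 stated. Then 68 × 6 = 408, and 408 / 0.75 = 544. None of this bears on uptake.

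**Inputs for the uptake check.**
- From Power calculations and sample size: target N of 600 (taken as 300 per arm), mean cluster size 100, ICC 0.001, CV 0.5.
- From the analysis section: alpha 0.05, read as two-sided.
- Assumed, because the protocol gives no figures: uptake in women who came for family planning (pA), uptake in women only interested (pB), and the share s who came for family planning in each arm.
- No true effect, and no adjustment for visit reason.

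**Formulas.**
- Uptake in an arm = s·pA + (1 − s)·pB.
- Spurious difference = (s1 − s0) × (pA − pB).
- Design effect = 1 + ((1 + 0.5²) × 100 − 1) × 0.001 = 1.124, so effective n = 300 / 1.124 = 266.9 per arm.
- False-positive rate: two-sided normal approximation for two proportions.

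**One case in full.** Take pA = 0.80, pB = 0.30, and shares 0.80 (intervention) and 0.70 (control). Uptake is 0.70 and 0.65. SE = √((0.21 + 0.2275) / 266.9) = 0.0405, and 0.05 / 0.0405 = 1.235. The chance of a significant result is P(Z > 1.96 − 1.235) + P(Z < −1.96 − 1.235) = 0.235.

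| pA / pB (assumed) | Share who came for family planning, intervention / control (assumed) | Uptake, intervention / control | Difference (points) | False-positive rate |
|---|---|---|---|---|
| 90% / 70% | 75% / 70% | 85% / 84% | 1 | 6% |
| 70% / 40% | 80% / 70% | 64% / 61% | 3 | 11% |
| 90% / 50% | 80% / 70% | 82% / 78% | 4 | 21% |
| 80% / 30% | 80% / 70% | 70% / 65% | 5 | 24% |
| 80% / 30% | 85% / 70% | 72.5% / 65% | 7.5 | 47% |
| 90% / 30% | 90% / 60% | 84% / 66% | 18 | over 99% |

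The ends of the range are 0.05 × 0.20 = 1 point and 0.30 × 0.60 = 18 points. Swapping the shares reverses the sign. Within each limb the difference is zero in every row, so comparing like with like removes the artefact.

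**Would the planned covariate rule catch it?** In the 80% versus 70% case, an imbalance test on visit reason gives 0.10 / √((0.16 + 0.21) / 266.9) = 2.7, p about 0.007, well under the 0.20 threshold. For 75% versus 70% it gives 0.05 / √((0.1875 + 0.21) / 266.9) = 1.30, p about 0.19, so it would pass the screen only about half the time. Both results assume that visit reason is recorded and put through the screen.

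**The case against.** **Matching.** Pairing on the kinds of service sought aims directly at visit mix. That counts, but it balances clinic populations rather than enrolled women, there are only three pairs, and the described model has no pair term. The protection is partial.

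**The p < 0.20 rule.** The text refers to any characteristic associated with treatment. If visit reason were recorded and screened, a 10-point shift would almost certainly be noticed, and a strong predictor would probably survive selection. But the preceding sentence ties the screen to demographics, visit reason is on neither list, and backwards selection may drop a candidate. The rule may help but does not secure the adjustment.

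**Assumed sizes.** This is correct. No rate in the table comes from the protocol, and the mild case barely moves the error rate.

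**A stronger reading.** A reader might infer that reception staff, knowing the arm, choose whom to refer and that this leaves no trace. The documents do not support that:
- As written, the receptionist offers the study to female patients under one neutral label, with no filter on visit reason. The research assistant, not the desk, applies criterion (a).
- The blinding statement, "No blinding of participants or providers will occur", does not mention reception staff. Their knowing the arm is plausible but inferred.
- The research assistants' training "provides education on the ARCHES intervention, RC and IPV", so they know the programme, but that is not evidence of selective enrolment.
- The accrual summary, "From each clinic, women will be approached for study recruitment; women will be excluded in the enrollment due to ineligibility or because they declined to" join, is brief and points to a figure not shown. Being approached may include the desk's offer, and a journal article may leave screening logs to the full protocol.

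The point does not need that mechanism: self-sorting by clinic is enough to make the mix differ, even with perfect recruitment.

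**Conclusion.** The point holds in a limited form. Followed as written, the plan can turn a difference in visit-reason mix between arms into an apparent effect on uptake, because allocation is non-random, criterion (a) pools two groups, uptake has no baseline contrast, and no named covariate separates the groups.

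Size and direction are unknown. Under the assumed inputs, with no true effect and no adjustment, the artefact ranges from about 1 to 18 points. The false-positive rate is about 6% in the mild case and about 24% for a 10-point shift with 80% versus 30% uptake. These rates use a simple two-proportion approximation and an ICC the protocol chose for reproductive coercion, not uptake. They show scale and do not predict what the planned mixed model would report.

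The point is confined to uptake. It should not be carried over unchanged to coercion and violence, where the difference-in-differences contrast removes stable baseline differences. It is a cheap and worthwhile improvement, and it is not evidence that recruitment was mishandled.

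**What to change.** 1. At screening, record which limb of criterion (a) each woman meets: came for family planning, or came for something else and is interested in it.
2. Prespecify this variable as a fixed covariate in the uptake model, exempt from the p < 0.20 screen and from backwards selection.
3. Report the split between the two limbs by arm.

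The cost is one screening field and one model parameter. The abstract describes the trial as under way. If the screening form already separates the two limbs, only the analysis text changes; if it does not, women enrolled before the field is added will lack the value, and the report should say how many.

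The adjustment deals with visit reason only. Other differences between non-randomised clinics remain, and the uptake result should be interpreted with that stated.
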